# Move-PCD—a multi-center longitudinal randomized controlled superiority trial on the effect of a 6-month individualized supported physical activity (PA) program on quality of life (QoL) in children, adolescents, and adults with primary ciliary dyskinesia

**DOI:** 10.1186/s13063-024-08379-0

**Published:** 2024-08-15

**Keywords:** PCD, Standard therapy, Physical fitness, Motor skills, Physical activity program

## Abstract

**Background:**

Primary ciliary dyskinesia (PCD) is a rare genetical disease with malfunction of the motile cilia leading to impaired muco-ciliary clearance in the respiratory tract. There is no cure for PCD, only supportive therapy aimed at minimizing the progression of the disease and improving the patient’s quality of life (QoL). Physical activity (PA) is one of these recommended supportive therapies for people with PCD (pwPCD). However, there is no scientific evidence to support this recommendation. In addition, regular medical advice to increase PA remains largely ineffective in pwPCD.

**Methods:**

To test the main hypothesis, that an individualized and supported PA program leads to a better QoL 6 months after randomization (QoL-PCD questionnaire) compared to usual recommendation in pwPCD, 158 pwPCD aged 7 to 55 years are to be included in this multi-center randomized controlled trial (RCT). After the screening visit, a 1:1 randomization stratified by age group and FEV1 will be performed. A QoL-PCD questionnaire, motor test, and lung function will be carried out at regular intervals in both groups. PA is recorded in both groups using activity trackers during the study period. The main aim of the trial is to estimate the difference in the change of QoL between the groups after 6 months. Therefore, our full analysis set consists of all randomized patients and analysis is performed using the intention-to-treat principle. Statistical software R (http://www.r-project.org) is used. Ethical approvement without any reservations: RUB Bochum Ethics Committee (No. 23–7938; December 4, 2023). Recruitment start: March 2024.

**Discussion:**

Limitations result from the rarity of PCD with its broad disease spectrum and the large age range. These are reduced by stratified randomization and the measurement of the individual change in QoL as primary endpoint. In our view, only a PA program tailored to individual needs with close contact to trainers offers the chance to meet personal needs of pwPCD and to establish PA as a pillar of therapy in the long term. The study protocol explains all procedures and methods of recruitment, implementation of the study visits and intervention, measures for patient and data safety, and for minimizing risks and bias.

**Trial registration:**

German Clinical Trials Register (DRKS) 00033030. Registered on December 7, 2023. Update 10 July 2024.

**Study protocol version 10:**

Version 1.2; 12 June 2024

**Supplementary Information:**

The online version contains supplementary material available at 10.1186/s13063-024-08379-0.

## Introduction

### Background and rationale

Primary ciliary dyskinesia (PCD) is a rare genetical disease characterized by malfunction of the motile cilia leading to impaired muco-ciliary clearance in the respiratory tract. More than 50 different gene mutations causing different ciliary defects are already known, which explains the heterogeneity of the disease. A chronic inflammation leads to loss of lung function and irreversible lung damage. There is no cure for primary ciliary dyskinesia, only supportive therapy, which aims to mitigate the progression of the disease as much as possible and improves the patient’s quality of life (QoL). Many of the therapy recommendations originate from the therapy of people with cystic fibrosis (pwCF). Physical activity (PA) is also recommended as a therapy for people with PCD (pwPCD). Along with respiratory physiotherapy, it is already one of the essential pillars of therapy [1–6]. However, regular recommendations by the physician to increase physical activity remain mostly ineffective.

As far as we know, no studies exist on long-term impact of physical activity on QoL, lung function, and survival for pwPCD [3, 7]. This randomized, multi-center control trial will be the first to determine the effects of improving motivation to exercise, i.e., of individualized and supervised PA over 6 months in pwPCD on QoL and clinical outcome. Based on clinical practice and experience from studies with pwCF [8–10], we assume a significant improvement in QoL as well as a slowing of disease progression through regular and, above all, mentored PA. This study could thus close the evidence gap for PA as part of PCD therapy and lead to improved adherence to PA in pwPCD.

Physical activity and aerobic fitness of pwPCD is significantly lower than in healthy individuals [11, 12]. In children with PCD, cardiopulmonary fitness is equally and consistently reduced as in pwCF [5]. In addition, lower physical performance is known to be associated with reduced lung function [2].

As we know from studies in pwCF, external motivation is essential for adherence to exercise [13]. The international study ACTIVATE CF about PA in pwCF concluded that pwCF need to be motivated to be physically active without pressure but with adequate support to build positive long-term activity behavior [9]. The CFmobil study demonstrated the benefits of an individually adapted and supervised long-term physical activity intervention for motor performance in children and adolescents with CF. It could be shown that motor skills improved during the 6-month intervention phase of the study but stagnated afterwards [13–15]. The results suggest that an individually adapted, guided, and regularly performed exercise program should include all aspects of physical fitness [13, 15]. In addition, health-related QoL in pwCF is linked to physical fitness [8–10, 16–18].

Sonbahar-Ulu et al. were the first to analyze the influence of PA in pwPCD. They demonstrated a positive effect of PA for 6–18-year-olds on lung function and QoL using active video gaming over 8 weeks [19, 20], but there are no studies on long-term effects of physical activity on QoL, lung function, and survival for pwPCD [3, 7]. According to the therapy guidelines, PA is recommended for pwPCD, but without scientific evidence.

We searched for evidence using the electronic databases for the keywords “primary ciliary dyskinesia,” “cystic fibrosis,” “bronchiectasis,” “physical activity,” and “quality of life.”

### Objectives

Against this background, the aim of this study is to evaluate the efficacy of PA in pwPCD. Based on clinical practice and experience from studies with pwCF [8–10], we assume a significant improvement in QoL as well as a slowing of disease progression through regular and, above all, mentored PA. This study shall close the evidence gap for PA as part of PCD therapy and lead to improved adherence to PA in pwPCD.

The main hypothesis of the trial is as follows: The support from an individualized and supported PA program results in higher PA and hence in a better quality of life 6 months after randomization (measured by physical functioning domain of QoL-PCD questionnaire) compared to treatment as usual in pwPCD with sole recommendation for PA (Table 1).

**Table 1 Tab1:** Objectives and endpoints

Objectives	Endpoints	Justification for endpoints
Primary		
To improve quality of life after 6 months of individual physical activity	Quality of life (physical functioning domain of the QoL-PCD questionnaire)	Well-established patient-relevant outcome
Secondary		
To evaluate the effect of the intervention on lung health, physical activity and fitness, as well as safety	Lung function parameters (VCmax (maximum vital capacity), FVC (forced vital capacity), FEV1 (forced expiratory volume in 1 s), PEF (maximum expiratory flow or peak flow), MEF 75/25 (maximum expiratory flow at 75/25% of FVC), sReff (specific airway resistance, if available), TLC (total lung capacity, if available)), Lung Clearance Index (LCI), if available	Relevant surrogates for health status and physical fitness of pwPCD with a chronic lung disease
	Physical fitness (motor test)	
	Physical activity (step count via activity tracker Garmin Vivo fit 4®)	Detection of the mechanism of action
	Quality of life (overall and single domains of the QoL-PCD questionnaire)	Detailed analysis of a well-established patient-relevant outcome
	Adverse events	Safety of intervention must be established

### Study design

The main hypothesis will be tested in a multi-center, parallel group, randomized controlled superiority trial (RCT). Randomization 1 will be done on patient-level. This RCT is used for investigation of the efficacy of PA in pwPCD.

## Methods

### Study population

The aim is to recruit a population of people with PCD in seven study centers in Germany, all of which are experienced in the care of pwPCD, and with the support of the patient organization “Kartagener Syndrom und Primäre Ciliäre Dyskinesie e.V.” (e.g., from the 2024 PCD Patient Congress).

The participants in the study should be able to perform a PA program safely, to perform the motor tests reliably, and to have a certain level of media literacy and a sufficient attention span to complete the online PA courses. The study centers require a PCD outpatient clinic with physicians experienced in care, the possibility of ECG, and pulmonary function diagnostics.

#### Inclusion criteria

To be eligible to participate in this study, an individual has to meet all the following criteria:Children and adolescents ≥ 7 years and adults ≤ 55 years oldConfirmed diagnosis of primary ciliary dyskinesia according to ERS criteria [21] (PCD confirmed or highly likely)Signed and dated informed consent form of the participants and of the guardian (in case of minors)Willingness to participate in the activity program and weekly phone contacts, and to wear the activity tracker for 1 year

#### Exclusion criteria

Meeting one of the following criteria leads to an exclusion of this study:Disability to take part in a PA program due to medical or other conditions [22–28]Decompensated heart failureCor pulmonaleHypertrophic cardiomyopathyArterial hypertension that is not normal under medical therapyMyocarditis in the last 6 monthsUnstable/progressive angina pectoris (e.g., new onset of angina, increase in symptoms, more need for medication)Uncontrolled arrhythmias (e.g., recurrent ventricular tachycardia, tachyarrhythmias, atrial fibrillation)Medium- to high-grade cardiac vitals, especially of the left heart (high-grade or symptomatic aortic valve stenosis, high-grade mitral valve insufficiency)Heart attack in the last 3 months incl. PTCA (percutaneous coronary intervention)Heart operations (incl. pacemaker/ICD operation in the last 3 months)Apoplexy in the last 5 yearsMarfan/Ehlers-Danlos syndromeUncontrolled bronchial asthma (i.e., on-demand medication more than 2 days a week or nocturnal symptoms)Lung transplantation (also planned)Respiratory partial insufficiency with intermittent or continuous oxygen therapyContinuous NIV (non-invasive ventilation)Hemato-oncological diseases currently under therapyPhysical inability to participate in PA or orthopedic limitations that preclude participation in the motor test battery or inclination to fallAny condition, fact, or comorbidity for which, in the opinion of the study investigator, study participation is not possible to participate, which represent an additional risk for study participation or lead to a falsification of the resultAlcohol or drug abusePregnancy (during the study drop-out criterion)Physical complaints on exertionDyspnea beyond the expected levelSyncopeChest pain/nauseaTendency to fall (including musculoskeletal)Examination results leading to exclusion (see “Screen failures”)Missing foot pulsesCentral cyanosisST elevation, AV block of grade II or higher, Long-QTFEV1 < 30%sO2 < 90%Participation in another intervention trial

#### Screen failures

Screen failures are defined as participants who consent to participate in this study but are not subsequently randomized. Minimal information on demography, screening failure details, and eligibility criteria will be given on the screening log. Screen failures due to medical contraindications may receive a recommendation for further medical clarification and counseling.

Individuals who do not meet the criteria for participation in this study (screening failure), but who are suspected during screening to be more eligible after some time, e.g., because expected therapy effects will occur or an acute infection will have been cured, can be rescreened after 4 weeks and will be classified as “re-screening required before randomization.” Examples include termination of participation in another clinical trial or clinical examination results, such as exacerbations score according to Lucas ≥ 3 [29]. Rescreened participants will be assigned the same participant number as for the initial screening.

### Strategies for recruitment and retention

In the 7 study centers, 280 pwPCD are regularly supervised annually. According to these study centers, 193 of these pwPCD meet the inclusion criteria, so that recruitment of 100 participants is realistically feasible.

Patients will be informed by flyers and posters in their outpatient department. In addition, patients will be recruited through the patient organization “Kartagener Syndrom und Primäre Ciliäre Dyskinesie e.V.” (200 association members with PCD) and the annual patient congress (on average 40–50 participants with PCD in all age groups).

Recruitment procedures will differ between hospitals and the congress setting. Recruitment should fit as well as possible into the respective clinic’s daily routine and the congress program to ensure feasibility and success. The procedure described below will therefore be adapted to the conditions in the respective setting; screening manuals will be written. To allow an analysis of the feasibility of recruitment, numbers (*N*) of patients screened in the different steps shall be documented in a screening log.

#### General procedure in the hospital

In the seven study centers, eligible patients will be informed about the study by a study physician of the center during a regular follow-up visit. If this discussion (pre-screening) does not reveal any further exclusion criteria, the patient can be included in the study. After verbal and written information, written consent for study participation is obtained (in the case of minors, by the legal guardian) at pre-screening or at least at the beginning of the screening visit. If exclusion criteria arise during the screening visit, the patient will be classified as “non-participating” and will not be randomized. The screening visit data will be stored in the central study database and analyzed if the participant does not actively object to this. Re-screening is possible in case of remediable findings, for details see “Screen failures.” Participants for whom all inclusion criteria and no exclusion criteria apply are classified as “eligible to participate” and are randomized at the earliest 2 weeks after the motor test as part of the baseline examinations.

The dates for the following study visits are assigned by the study centers in coordination with the dates for the motor test by the training institute [name]. [name]. Whenever possible, the study visits should be combined with regular outpatient appointments.

#### General procedure for recruitment via the patient organization

Recruitment as part of the patient congress

With the registration confirmation for the 2024 patient congress in Hamburg, the patient organization will send a reminder for the study. The inclusion and exclusion criteria are again pointed out here and congress participants are asked to bring all medical documents including cilia and genetic findings to the congress, if interested in study participation. This is necessary to be able to decide about eligibility for study participation at the congress. Congress participants who could take part in the study according to the inclusion and exclusion criteria will be informed verbally and in writing. After written information has been provided (see above), the screening visit including the motor test will be carried out on the same or following day. For the follow-up visits, appointments are either made at the lead study center in Bochum or the participants agree to a telephone visit. In this case, an examination close to home, including pulmonary function tests, is required by the treating doctor, for whom a confidentiality agreement must be in place. The following motor tests are carried out close to home after an appointment has been made with the training institute. The rest of the procedure corresponds to that in the study centers (see above).

b)Recruitment via mailing list or homepage

If a pwPCD contacts the central study center Bochum via advertising on the homepage or via the email distribution list of the patient organization, they will receive telephone and written information about the study. The inclusion and exclusion criteria will be checked in a telephone conversation. If participation in the study is not excluded in principle, an appointment will be made in Bochum for the screening visit and the motor test. Both will take part as described above for congress participants.

#### Procedures to enhance participant retention and motivation

All visit data are entered into the central database. The participants receive an automatic reminder email 1 week before the appointment. To improve adherence, all participants will also receive an automatic email once a month thanking them for taking part in the study (e.g., “It’s nice that you are part of the MOVE-PCD study”) and reminding them to wear the activity tracker. For added motivation, the online PA courses can continue to be taken at any time after receiving the release link, even beyond the intervention period. This also applies after the V4 has been reached for the control group.

### Study intervention

The intervention group receives an individualized PA program for 6 months considering personal preferences as well as the current state of fitness. The individual training plans are compiled by sports scientists with long-term experience in exercising with chronically ill people [30, 31]. The participant has the option of expanding his or her PA program at any time and is provided with additional training content for this purpose. To keep the entry threshold for training as low as possible, no minimum duration or frequency per week is specified. Nor are there any specifications regarding the weighting of endurance, strength, coordination, or mobility; instead, the patient’s wishes are considered. For standardization, the intervention consists of weekly online or telephone consultations with a personal coach. Possible topics to be discussed are implementation of the individual training plan, motivation, adaptation of the training as well as barriers to physical activities and their management.

In addition to the individual training plan, each week three different online courses are offered (1. Enjoy the day: mixture of flexibility, strengthening, and relaxation elements. 2. Strengthen the body: focus on strength build-up. 3. Move the rhythm: movement choreography). The advantage of the online PA courses, apart from hygienic aspects (no transfer of resistant pathogens), is that they can be implemented flexibly in terms of time and allow participants to enter the study at any time, even though the courses build on each other.

The intervention is based on the theory that personalized, regular, and individualized care in pwPCD will significantly increase and improve PA, thereby increasing treatment adherence to the extent that it has relevant effects on QoL and disease progression.

Standard therapy with inhalations of high-percentage saline and antibiotics, respiratory physiotherapy, nasal rinses, and oral intake of medications such as antibiotics and proton pump inhibitors are allowed. The standard therapy should not change relevantly during the study period.

If a medical condition during the study is decreased leading to inability to take part in PA, the patient has to stop the intervention but will be encouraged to complete at least the assessment of the primary efficacy endpoint.

#### Scientific rationale and justification for study design

To receive a high level of evidence, a randomized controlled trial is necessary. The study intervention is compared to the current standard of care [2]. Participants allocated to the control group receive treatment as usual with the mere recommendation to be physically active. Only by comparing standard therapy with individual PA in pwPCD is it possible to evaluate the effect on quality of life in PCD.

The duration of the intervention results from the fact that the physical activity of chronically ill people must be increased gradually and that the positive effects only appear after weeks of regular activity. However, this can be interrupted again and again in people by a worsening of the underlying disease, among other things. Participants may pause for a few days or weeks and then resume activity at a reduced level. Measuring the success of the intervention after a few weeks would therefore not be meaningful.

An evaluation of the success of the intervention after 6 months allows the assessment of the patients’ longer-term motivation for PA, and the ability of the qualified trainers to maintain this motivation, reduce barriers, strengthen resources, and thus initiate a sustainable behavior change in pwPCD.

We deliberately refrained from offering the control group the same number of personal contacts in order not to distort the intervention effect. Our study tests the effectiveness of a complex PA intervention in a real world setting against the current standard of care.

To also offer the control group a benefit of the study without confounding the outcome, all participants in the control group will receive access to the online PA courses after their last study visit (V4). It is up to the participants themselves whether and to what extent they use the offer.

#### Fidelity—interventionist training and tracking

The training institute [name]. [name], consisting of sports scientists, sports physiotherapists, and physiologists experienced in training and research with patients with chronic lung diseases such as COPD [30, 31], develops individual training plans based on the results of the baseline motor tests and questionnaires. The assessors will all be trained for a standardized performance of assessments and tests. The team around [name]. [name] also carries out the weekly contacts to review and, if necessary, adjust the training plans and determine the safety of the intervention. The conversations are documented in the central database and will be standardized. Prior to the start of the study, [name]. [name] will instruct all employees on the special features of the disease PCD. During the intervention phase, a weekly online conference of all personal coaches is planned to exchange experiences. Critical cases or difficulties with coaching are discussed immediately with [name]. [name].

#### Study intervention adherence

A large part of the intervention consists of weekly appointments with personal coaches. These also serve to document and check the adherence of the participants.

#### Study intervention discontinuation and participant discontinuation/withdrawal

The occurrence of diagnoses or examination results listed under “Exclusion criteria” or a positive answer in the weekly safety query described under “Safety assessments” will lead to an immediate discontinuation of the intervention.

When a subject discontinues from the PA program but not from the study, remaining study procedures will be completed as indicated by the study protocol. In individual cases, a decision may be made to continue the study without participation in the assessment of physical fitness.

In addition, all subjects are explicitly informed that if they have any doubts about PA and exercising, they should discontinue and contact the supervising or leading study center. Participants will be informed that if one of the following symptoms occurs, PA must be interrupted, or no further PA should be done until medical clarification is obtained:Fever or other infections accompanied by a feeling of illnessAcute pulmonary exacerbationSevere joint, back, or head pain during or immediately after exerciseChest pain or left arm painDizziness/syncopeShortness of breath (beyond expected level) or hyperventilationHypoglycemiaPersistent palpitations or heart palpitations after exercisePacemaker/ICD depending on type of PA

Participants are free to withdraw from participation in the study at any time upon request without giving reasons and without suffering any disadvantage, as stated to them prior to informed consent. Participants will be given the choice as to whether their withdrawal will only be from further contact from the trial team or withdrawal of all their unanalyzed data.

An investigator may discontinue a participant from the study for the following reasons:Lost-to-follow up; unable to contact subject (see below)Any event or medical condition or situation occurs such that continued collection of follow-up study data would not be in the best interest of the participant or might not be possible, e.g., longer inpatient stay

The reason for participant discontinuation or withdrawal from the study will be recorded on the study discontinuation form. Subjects who sign the informed consent form and are randomized but do not receive the study intervention may be replaced.

A participant will be considered lost to follow-up if he or she fails to return for one scheduled assessment and study staff are unable to contact the participant after five attempts.

The following actions must be taken if a participant does not return the required assessment:The site will attempt to contact the participant, within 1 week, counsel the participant on the importance of maintaining the assigned assessments and, if possible, will perform the assessment by telephone. Furthermore, the site will ascertain if the participant wishes to continue in the study.Before a participant is deemed lost to follow-up, the investigator or designee will make every effort to regain contact with the participant (where possible, 5 telephone calls, or 3 calls and two times a certified letter to the participant’s last known mailing address). These contact attempts will be documented in the participant’s medical record or study file.Should the participant continue to be unreachable, he or she will be considered to have withdrawn from the study with a primary reason of lost to follow-up.

If, for medical reasons (e.g., pulmonary exacerbation), one of the study visits cannot take place on the scheduled date, it can be made up for within a maximum of 4 weeks.

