The questionnaire is an established, validated instrument and used as an outcome parameter in several studies and in the international PCD registry [38, 39]. The QoL-PCD exists for all ages and contains a child version (37 items, 7 scales), parent proxy version (41 items, 9 scales), adolescent version (43 items, 7 scales), and adult version (49 items, 10 scales) [38–40]. The QoL-PCD scales include physical functioning (primary outcome); the other ones are secondary endpoints (e.g., emotional functioning, treatment burden, social functioning, role functioning, health perception, vitality). With the QoL-PCD, we choose an internationally validated PCD specific tool for different age groups [38, 39]. Filling in the questionnaire takes little time and will be tablet based or may be done at home via an individual link. One week before randomization, the participants and, in the case of minors, also the guardians receive a link with which they answer the questionnaire directly online in the central database. In addition, the questionnaires are recorded during the V2–V4 visits after 3, 6, and 12 months.

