#### Sample size determination

For the physical domain of the QoL-PCD 15.2 points were proposed as minimum clinically significant change, the observed standard deviation (sd) in a similar patient group was 30.4 [38]. Sample size calculation for a two-sided two-sample *t*-test at a significance level (*α*) of 5% resulted in a required sample size of 64 per group to reach a power of approximately 80% to detect an effect size of 0.5 (15.2/30.4). Assuming a drop-out rate of 5%, 158 participants should be recruited.

PCD is a rare disease for which there are few specialists. Medical research in PCD and especially in therapy has made little progress to date. Many pwPCDs therefore have a great interest in clinical research and a close bond with their practitioners and travel long distances to do so. We can therefore expect a high level of compliance.

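### A participant unreachable after one missed visit is classed as withdrawn, possibly at month 3, and no renewed approach for the 6-month primary outcome is described

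*Protocol article*

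**What the plan says.** The rule stands in the Protocol article under Study intervention discontinuation and participant discontinuation/withdrawal. A person is "considered lost to follow-up if he or she fails to return for one scheduled assessment and study staff are unable to contact the participant"; the number of attempts required is five. The site must first try to make contact within a week, offer a telephone assessment where possible, and make further attempts (where possible five calls, or three calls and two certified letters). If these fail, "he or she will be considered to have withdrawn from the study with a primary reason of lost to follow-up".

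Other relevant statements in the same article:

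- **Timing.** The QoL-PCD is collected before randomisation and at V2, V3 and V4 (3, 6 and 12 months). The primary endpoint is its physical functioning domain at 6 months.
- **Mode.** Under QoL questionnaire, completion is by tablet or "may be done at home via an individual link".
- **Contact by arm.** Under Study intervention, "the intervention consists of weekly online or telephone consultations with a personal coach". Under Scientific rationale and justification for study design, controls are deliberately not given the same number of personal contacts.
- **Expected loss.** The Discussion names frustration and higher drop-out among controls as a risk to be counteracted. Sample size determination says: "Assuming a drop-out rate of 5%, 158 participants should be recruited".
- **Missing data.** Under Analysis of the primary endpoint, a missing primary outcome is multiply imputed from baseline and later available data, in an intention-to-treat analysis.

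**The concern.** The rule ties the end of study participation to a single missed visit with failed contact, not to a withdrawal of consent. Applied at V2, it can close follow-up about three months before the primary outcome is due. That outcome is a questionnaire that needs no visit, and the link and automated e-mails already exist.

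At stake are primary outcomes that go missing because they were not requested. The people concerned would usually lack the month-3 score as well, which is the most informative post-baseline value for imputing month 6. The trial is unblinded and the outcome is patient-reported, so people who fall silent may differ from those who stay in ways that baseline does not explain. If the two arms lose people at different rates or for different reasons, the treatment comparison is affected.

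**Working it through.** **1. Order of events.** V2 is at 3 months and V3 at 6 months, each within 2 weeks either way by the note to the schedule of activities. A visit postponed for medical reasons can be made up within 4 weeks. Contact attempts begin within 1 week of a missed assessment. The classification can therefore be complete well before V3 opens.

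**2. Ways of leaving, side by side.**

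| Situation | What the article provides |
|---|---|
| Stops the programme but stays in the study | Remaining study procedures are completed |
| Medically unable to continue the activity | Encouraged to give at least the primary endpoint |
| Withdraws by own decision | Chooses between no further contact and removal of unanalysed data |
| Misses one visit and cannot be reached | Considered withdrawn; nothing is said about month 6 |

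Only the last group has neither made a decision nor been given a route to the primary outcome.

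**3. The plan's sample size.** Inputs from Sample size determination: difference 15.2, SD 30.4, two-sided 5% level, power about 80%.

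- Normal approximation: 2 × (1.960 + 0.842)² / 0.5² = 62.8, so 63 per group. The exact t-test gives 63.8, so 64, with power 80.1%. The stated 64 is reproduced.
- Inflation: 128 / 0.95 = 134.7, so 135, or 136 with equal arms. The stated 158 is not reproduced; it corresponds to 1 − 128/158 = 19% loss. That is a separate matter. It bears on this point only because 158 leaves a margin above 128.

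**4. Power under unequal loss.** Assumptions: 79 randomised per arm, completers only, effect size 0.5. The loss rates are assumed, since the documents give none by arm.

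| Loss, intervention / control | Completers | Power |
|---|---|---|
| 5% / 5% | 75.05 / 75.05 | 86.1% |
| 5% / 10% | 75.05 / 71.1 | 85.1% |
| 5% / 20% | 75.05 / 63.2 | 82.8% |
| 5% / 30% | 75.05 / 55.3 | 80.0% |

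Power is not the problem.

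**5. Possible bias.** Let p be the share of controls without a primary outcome, and D the amount by which they differ from retained controls beyond what imputation explains. Assume no such gap in the intervention arm. The control mean is then off by p × D, and so is the treatment difference.

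- 5% × 5 points = 0.25 points
- 10% × 10 points = 1.0 point
- 20% × 15.2 points = 3.04 points

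Against the 15.2-point target these are 1.6%, 6.6% and 20%. The sign depends on whether the lost controls fare worse (effect understated) or better (effect overstated). Both p and D are assumptions, and p covers loss from any cause. A change of rule can reduce only the part that comes from people who would still answer at month 6.

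**The case against.** **The rule is not hasty.** It takes a missed assessment and several failed attempts, with a telephone assessment as fallback and certified letters as an option. Few people may meet it. This stands and limits the size of the problem.

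**A reader might infer that these participants are never asked for the 6-month outcome.** The text does not say so. Reminders and monthly e-mails are described for participants without exception, no sentence switches off the link, and an investigator may, not must, discontinue someone lost to follow-up. The article stops data collection expressly only when consent is withdrawn. Against this, the two sentences that classify the participant are worded as definite, and nothing describes a later approach. The gap is real, but it is a gap and not a stated bar.

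**A reader might infer that the rule removes mainly controls, who receive nothing but automated e-mails.** The documents do not support this either. The rule is the same in both arms, and both arms have visits, motor tests and synchronised trackers. The Discussion names a control-arm risk without a rate and without linking it to this rule. What stands is that unequal personal contact makes unequal loss plausible.

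**A reader might want a count of recoverable outcomes.** If 5% to 10% were unreachable at V2 and half answered a link, that would be 158 × 0.05 × 0.5 ≈ 4 to 158 × 0.10 × 0.5 ≈ 8. Neither input is in the documents. The upper rate is twice the whole drop-out allowance, and half is hard to defend for people who have not responded to five attempts. The count should not be relied on.

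**The full protocol or analysis plan may settle it.** Imputation details belong there, and operational timing may too. But this is a conduct rule that the article states, and no analysis recovers data that were not requested.

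**Conclusion.** The concern holds as a weakness in a stated conduct rule. Followed as written, the rule lets a participant be treated as withdrawn from about month 3 without having withdrawn consent, and it leaves a 6-month approach to each centre. This sits poorly with an intention-to-treat primary analysis and with the provision made for those who stop the activity for medical reasons.

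The consequence is possible bias from missing outcomes that may differ by arm. Its size cannot be estimated from the documents. The illustrative range of 0.25 to about 3.0 points rests wholly on assumed loss rates and assumed unexplained differences. Power is not threatened at the stated 158.

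**What to change.** Replace the rule so that a missed visit with failed contact does not by itself end study participation. Suggested content: unless consent or further contact is withdrawn, every randomised participant in either arm is sent the V3 and V4 QoL-PCD links and reminders on the scheduled dates. A participant is classed as lost for the primary endpoint only after the V3 window has closed. The contact attempts after a missed visit can stay as they are.

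The cost is a short amendment and a few extra automated messages to people who do not reply. The links and e-mails are already part of the trial, and the sample size and analysis model do not change.
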